## Abstract

**Background.** Parkinson's disease (PD) leads to cognitive dysfunction which limits participation and occupational performance. Cognitive Orientation to Daily Occupational Performance (CO-OP) approach is effective in other adult neurological populations and warrants investigation in PD. **Purpose.** To describe a study protocol evaluating the preliminary efficacy and feasibility of CO-OP approach in PD. **Method.** A randomised controlled trial (RCT) with adults with PD was assigned to either: CO-OP training-intensive (CO-OP-I, 20 sessions) or waitlist control (WLC) followed by CO-OP-standard (CO-OP-S, 10 sessions). **Outcomes.** Occupational performance and satisfaction of adults with PD in chosen goals. Measures will be obtained at baseline, post-intervention, and 3-month follow-up. **Implications.** As the first RCT focused on CO-OP in PD, this trial will provide evidence for the potential of this approach in PD and lay the groundwork for future large-scale trials. **Trial Registration.** Australian New Zealand Clinical Trials registry, ACTRN12621001483842. Registered November 1, 2021; retrospectively registered 3 months after commencement.

## Introduction

Parkinson's disease (PD) is a chronic, progressive, incurable, complex, and disabling neurological condition (Access Economics & Parkinson's Australia, 2007). Following dementia, PD has the second highest prevalence and mortality rate of all neurological conditions (Pringsheim et al., 2014). Despite major advances in the treatment and understanding of PD pathophysiology, people with PD have persisting problems with functioning and participation in meaningful activities, self-efficacy, and quality of life (QoL). There is a need to find novel approaches to help people with PD maximize their QoL, function, and participation (Chaudhuri & Titova, 2019).

PD is classified as a movement disorder that occurs due to the degeneration of neurons in a region of the basal ganglia known as the substantia nigra (Tysnes & Storstein, 2017). The hallmark motor symptoms of tremor, rigidity, bradykinesia, and postural instability are progressive and contribute significantly to disability (Chrischilles et al., 1998). Hariz and Forsgren (2011) evaluated the activities of daily living (ADL) performance and QoL in 99 newly diagnosed people with PD. People with PD were found to have more difficulties in 25%–50% of personal ADL tasks (eating, un/dressing, bathing, showering, writing, and nail care) and in 75% of instrumental ADL tasks (cooking, grocery shopping, cleaning, and laundry) compared to healthy controls. Whilst treatments focusing on motor impairments are the subject of numerous studies, needs in other areas arising from PD symptomology have largely remained unmet and under-researched (Chaudhuri & Titova, 2019).

Alongside motor symptomology, people with PD also experience significant non-motor symptoms, particularly cognitive dysfunction (Aarsland et al., 2009; Cahn et al., 1998; Dalrymple-Alford et al., 2011; Dirnberger & Jahanshahi, 2013; Verleden et al., 2007). Importantly, non-motor symptoms often precede motor symptoms, having a hidden but significant impact on everyday functioning. A large, multi-centre study by Aarsland et al. (2009) found cognitive dysfunction was a key feature from the time of diagnosis of PD, with nearly 20% of 196 newly diagnosed and unmedicated people demonstrating mild cognitive impairment (MCI). Cognitive dysfunction in PD is also progressive. An Australian, multi-centre longitudinal study of 135 people found that dementia was present in 83% of people 20 years after diagnosis (Hely et al., 2008). Cognitive impairment and dementia associated with PD represent a major management challenge and area of unmet need (Burn et al., 2014).

Research indicates that cognitive defects in PD are typically frontostriatal in nature (Lewis et al., 2003). The most frequently reported cognitive symptom is impaired executive functioning (EF) (Esteves et al., 2018). EF refers to the complex cognitive processing requiring the coordination of several subprocesses to achieve a particular goal (Elliott, 2003; Singer & Chen, 1994). Studies of individuals with PD but without dementia or depression reliably show impaired EF with planning, sequencing, working memory, and set-shifting most affected (Emre, 2015). These EF skills are critical as they are necessary for the independent execution of a person's goal-directed behaviour; thus, impairments in EF impact independence, QoL, and psychological well-being (Dirnberger & Jahanshahi, 2013). Subjective reports of people with PD indicate that cognitive symptoms were perceived as more restricting in daily life than motor symptoms (Cahn et al., 1998). The non-motor complications of PD consistently are associated with worse QoL, poorer outcomes, increased caregiver burden, and increased risk of institutionalization, highlighting their clinical significance as an independent and high-priority area of research (Biundo et al., 2017).

Research evidence from other neurological populations, including traumatic brain injury (TBI), stroke, and MCI, supports the use of occupation-based, meta-cognitive interventions, especially those that are directed explicitly at improving a person's functioning in their everyday lives (Cicerone et al., 2019). Metacognition is “thinking about thinking” and incorporates knowledge, past experiences, goals, and strategies (Moritz & Lysaker, 2018). Occupations are all the daily activities that enable people to care for themselves, participate in family life, and contribute to broader society (Crepeau, 2003, page 28). Meta-cognitive, occupation-based approaches use a holistic, top-down rather than impairment focussed approach by applying strategy training and compensatory approaches to enhance the performance of meaningful activities or occupations. Strategy training, as described above, is recommended as a Practice Standard (highest strength of evidence) for rehabilitation of memory, attention, and executive function deficits in other populations, including brain injury (Cicerone et al., 2011), and early dementia (Clare et al., 2013). Importantly, it has been established that the cognitive impairment profiles and cognitive rehabilitation goals for people with PD are similar to these other populations. Therefore, occupation-based, meta-cognitive interventions warrant investigation for adults with PD (Hindle et al., 2016; Vlagsma et al., 2016).

Cognitive Orientation to daily Occupational Performance or CO-OP is “a client-centred, performance based, problem solving approach that enables skill acquisition through a process of strategy use and guided discovery” (Polatajko & Mandich, 2004, p. 2). CO-OP is an approach that is structured, manualized, and widely established as effective across multiple studies and populations (Dawson et al., 2013; Jacob et al., 2020; McEwen, 2009; Peny-Dahlstrand, 2020; Saeidi Borujeni et al., 2019; Scammell et al., 2016). CO-OP integrates functional skills training (occupation-based) and metacognitive strategy training through client-centred goal setting and the use of the global metacognitive strategy of “Goal-Plan-Do-Check” (Polatajko et al., 2001). Throughout the therapeutic intervention, people come to internalize the global strategy which enables new learning and problem-solving behaviours to emerge. To our knowledge, this is the first trial to investigate potential of the CO-OP approach for improving the function of adults with PD. An RCT will be conducted to determine preliminary efficacy and establish feasibility according to Bowen's framework (Bowen et al., 2009).

The primary objective is: (a) to investigate the preliminary efficacy of the CO-OP approach on goal attainment, skill transfer, perceived executive function, and functional performance for adults with PD; the secondary objective is (b) to explore participants’ perceptions of self-efficacy and health-related QoL through use of the CO-OP approach; the tertiary objectives are (c) to explore the feasibility and acceptability of the CO-OP approach for adults with PD; (d) to compare the primary and secondary outcomes and experiences of the CO-OP approach at varying program intensities, and; (e) to investigate the long-term maintenance of and generalization of skills for adults with PD at follow-up.

We hypothesize that adults with PD will experience (i) improved performance on trained and untrained goals, improved perceived executive function and functional performance following CO-OP compared to waitlist controls (WLC) and (ii) improved perceived self-efficacy, and health-related QoL following CO-OP compared to WLC; and that (iii) higher CO-OP intervention intensity will be feasible and acceptable, lead to better health outcomes and long-term maintenance and generalization of skills compared to standard CO-OP.

## Method

### Design and Setting

A parallel-group assessor-masked randomized controlled feasibility trial using blocked allocation (6 per block) to enable equal ratios between treatment and control groups. Intensive CO-OP (CO-OP-I) training will be compared to WLC to establish preliminary efficacy. Following a non-intervention period, the WLC will then undertake standard CO-OP (CO-OP-S) (Figure 1). A mixed-method approach will be used to assess feasibility in terms of acceptability, demand, implementation, practicality, adaptation, integration, expansion, and limited-efficacy testing (Bowen et al., 2009). The study was approved by the UQ Human Research Ethics Committee (HREC) — 2020/HE002650 on February 9, 2021.

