**Figure 1. fig1-00084174231156287:**
[figure not shown]
CONSORT style study flowchart.

This study conforms to the recommendations made by Biundo et al. (2017) for cognitive rehabilitation trials for people with PD where feasible. Recommendations include cognitive profiling, cognitive domains targeted, randomization methods, optimal delivery of neuro-rehabilitation approach, important outcome measure domains, and inclusion/exclusion criteria.

This study involves a person with PD as a consumer from the beginning of the research process to enhance the relevance and usefulness of the research to people with PD (Graham et al., 2018). The involvement of the consumer in this study was from the initial stages and discussions about roles was guided by the involvement matrix tool (Smits et al., 2020) which describes five roles: Listener, Co-thinker, Advisor, Partner, and Decision maker. Collaboratively agreed-upon roles for this project included Advisor and Co-thinker.

The intervention will take place in each participant's home environment in Brisbane, Australia. The first author, an experienced clinician with adult neurological populations trained in CO-OP approach (Polatajko et al., 2001) will collect the data and administer the intervention. The masked assessor is an experienced clinician who did not deliver the intervention and is masked to treatment condition and phase.

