### Procedures

The study will be advertised online on the Parkinson's Queensland Research Participation Opportunities page, on their social media platforms and via the member's newsletter. Potential participants will self-select and contact the interventionist if they are interested in participating in this research. During first contact via telephone, the interventionist will undertake eligibility and cognitive screening, provide participants with information about the study, and obtain verbal consent to participate. Potential participants will be emailed a copy of the participant information and consent form to aid their decision-making process with regards to study participation. Study participation will be offered if eligible and score above the cut-off for the telephone Montreal Cognitive Assessment (T-MoCA). Participants will be emailed the link to the online survey once the offer of participation is verbally accepted. The online questionnaire collects demographic and disease information and self-report outcome measures and will be completed independently by participants, outside session times. The interventionist will then complete a home visit to complete baseline assessments and program goal setting facilitated by the Canadian Occupational Performance Measure (COPM) will occur. Hard copies of the participant information and consent forms will be provided to participants during the first home visit, and written consent obtained. Using the prioritized goals identified during the COPM interview, Goal Attainment Scales (GASs) for each goal will be created to enable objective measurement by an independent assessor, according to the procedure used previously for the combined use of the COPM and GAS (Doig et al., 2010). Baseline performance in goal activities will be recorded objectively to enable independent ratings of goal performance by a masked assessor. Following this visit, participants will be randomly assigned to either the CO-OP-I or a WLC with a blocked equal allocation, stratified by scores on the Addenbrooke's Cognitive Evaluation – III (ACE-III), by a computer-generated randomization schedule. A summary of the timeframes for consent, screening, goal setting, randomization, and outcome measurement across the phases of the study are outlined in Table 1.

**Table 1 table1-00084174231156287:** Phases of Study

	Enrolment	Baseline	Intervention		Follow-up

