#### Demographic and Disease Data

Demographic and disease data collected at baseline via an online Qualtrics survey includes age, sex, education level, work status, disease duration, and medical management (i.e., levodopa dosage). Data collected in person during the initial home visit will include pre-morbid IQ, neuropsychological status, and disease severity.

The National Adult Reading Test (NART) (Nelson & Willison, 1991) is a 50-word reading test that provides reliable and valid estimates of IQ and has been shown to be relatively insensitive to the effects of various neurological conditions, including PD (Mathias et al., 2007). The NART will be used in this study to estimate the premorbid intelligence levels of participants to describe the study sample.

The ACE-III (Mioshi et al., 2006) is a brief cognitive screening battery assessing five neuropsychological domains (orientation and attention, memory, verbal fluency, language, and visuospatial function). The ACE-III score will be used to stratify participants for randomization. The stratification groups are no cognitive impairment and MCI. The cut-off score for this assessment will be 88 whereby a score of 100–89 is considered no cognitive impairment and a score of 88–77 is considered MCI (Senda et al., 2020).

The Modified Hoehn and Yahr (H&Y) scale (Hoehn & Yahr, 2011) is a 7-point Likert scale that focuses on the clinical impression of overall PD severity based on key aspects of disability and features of objective impairment. The H&Y scale will be used to measure disease severity/stage.

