## Goal Setting

Participants will identify four goals during goal planning. Participants’ three most important goals will be targeted in the CO-OP intervention. The fourth goal, which may be of lesser importance, will be an “untrained goal”, and measurement of performance on this goal will enable the determination of transfer and generalization of strategy use. GASs for each goal will be developed and documented for all four of the goals by the interventionist once baseline performance has been established, as per the guidelines outlined by (Turner-Stokes, 2009). Consideration will be given to the nature of the goal activities when formulating and agreeing on the specific goal. Feasibility, scope, environment, and time will be considered in goal selection and intervention.

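### With a single block size of 6, the interventionist who writes the GAS levels could deduce up to a quarter of allocations once the ACE-III stratum is known

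*Protocol article*

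**What the plan says.** **Allocation.** Design and Setting gives one block size, "using blocked allocation (6 per block) to enable equal ratios between treatment and control groups". Procedures confirms the ratio: "participants will be randomly assigned to either the CO-OP-I or a WLC with a blocked equal allocation". Demographic and Disease Data defines two strata by ACE-III score, 89–100 and 77–88: "The stratification groups are no cognitive impairment and MCI". Under Random Allocation, an independent senior team member generates the schedule with concealment and allocates in order of written consent.

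**The interventionist's roles.** Design and Setting says that the first author "will collect the data and administer the intervention". By telephone, "the interventionist will undertake eligibility and cognitive screening" (Procedures). The baseline visit belongs to the same person: "The interventionist will then complete a home visit to complete baseline assessments and program goal setting". Goal Setting says that the GAS levels are "developed and documented for all four of the goals by the interventionist", and Masking repeats that the interventionist sets the scoring criteria at baseline.

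**Sequence.** The ACE-III is done at that home visit: "Data collected in person during the initial home visit will include pre-morbid IQ, neuropsychological status, and disease severity". Randomisation follows the visit. The order of ACE-III scoring and goal setting within the visit is not fixed, although Procedures names assessments first.

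**The concern.** A concealed list protects against foreknowledge only if the next entry cannot be worked out from earlier ones. In a 1:1 block of 6, once one arm has its three places, every remaining allocation in that block is forced. Someone who treats all participants sees past allocations as they happen. With the block size and the current participant's stratum, that person can sometimes know the next arm for certain.

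Here that person also decides, just before allocation, what counts as the expected outcome on each GAS. A slightly easier scale for someone about to enter CO-OP-I, or a harder one for someone about to wait, would bias the between-group comparison. The later masked rating would not remove this bias, because the masked assessor applies whatever scale was written.

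**Working it through.** The article gives no sample size and no predictability figure, so there is nothing of its own to reproduce.

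**Inputs from the article:** block size 6; equal allocation, so 3 + 3 per block; two ACE-III strata. **Assumptions:** blocks run separately within each stratum; the observer knows the block size, the stratum and all earlier allocations.

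**1. Certain allocations in a complete block.** There are C(6,3) = 20 equally likely orderings. A position is certain when one arm already has its three.

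| Position | Orderings in which it is certain | Probability |
|---|---|---|
| 1, 2, 3 | 0 of 20 | 0 |
| 4 | 2 of 20 | 0.10 |
| 5 | 8 of 20 | 0.40 |
| 6 | 20 of 20 | 1.00 |

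Sum: 0.10 + 0.40 + 1.00 = 1.5 per block, and 1.5/6 = 25%. The closed form for a block of 2k is 2k/(k+1); with k = 3 this is 6/4 = 1.5.

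**2. Best guess.** Always naming the arm with more places left is right with probability 0.5, 0.6, 0.6, 0.7, 0.7 and 1.0 at positions 1 to 6. The sum is 4.1, and 4.1/6 = 68.3%, against 50% by chance.

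**3. Unfinished blocks.** The certain positions lie at the end of a block, so a stratum that stops mid-block has fewer of them. Take an assumed total of 24. Split 12/12, the share is (3.0 + 3.0)/24 = 25%; split 9/15, it is (1.5 + 3.0)/24 = 19%. Averaged over random stratum splits, assumed totals of 12 to 60 give about 15% to 23%. So 25% is a ceiling.

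**4. Stratum not yet known.** Averaged over positions, the next place in a stratum is forced to a given arm with probability 0.25/2 = 0.125. Without the stratum, the arm is certain only if both strata are forced to the same arm: 2 × 0.125² = 0.031, about 3%.

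**5. Effect of varying the block size.** Simulation with 24 allocations per stratum and 4,000 runs; the observer knows the set of sizes but not which one is in use.

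| Block sizes | Certain | Best guess correct |
|---|---|---|
| 6 only | 24.9% | 68.3% |
| 4, 6 | 5.7% | 68.6% |
| 2, 4, 6 | 3.9% | 69.9% |
| 4, 6, 8 | 2.2% | 67.3% |

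Varying the size removes most of the certainty and almost none of the guessing advantage.

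**The case against.** **Knowledge of the block size is inferred.** No sentence says that the interventionist knew it while enrolling. The inference rests on first authorship of the article that prints it, and the schedule is described as concealed. This stands as a condition on the finding. It does not dispose of it: a single fixed size is a stated design choice, and the article does not say it was kept from the person most able to use it.

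**Selective entry.** A reader might infer that foreknowledge could steer who is offered a place. The documented sequence gives little support. Participants volunteer, and the offer is made by telephone after the T-MoCA, before the ACE-III is done. With the stratum unknown, about 3% of allocations are certain.

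**Goals set with foreknowledge.** A reader might also infer that a quarter of allocations are known before goals are set. That holds only if the ACE-III is scored first, which the article does not fix, and only for complete blocks.

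**Breadth of harm.** The PDQ, NEADL and S&E do not depend on goal choice or scaling. COPM problems are chosen and scored by the participant. GAS has its baseline anchored at −1 and a masked rater, which narrows the interventionist's freedom. The expected level still has to be set, so some freedom remains.

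**Scale of trial.** This is a feasibility trial seeking preliminary efficacy. That limits the consequences, but the remedy is cheap.

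**Conclusion.** The point holds in a bounded form. Up to 25% of allocations (1.5 per complete block of 6) could be deduced before the GAS levels are final, despite the independent, concealed schedule. The realistic average is about 15–23% for assumed totals of 12 to 60. This rests on three conditions: the interventionist knows the block size, the ACE-III stratum is known before the GAS levels are finished, and blocks run within strata. If the stratum is unknown at that moment, the figure falls to about 3%.

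The exposure is to the goal-based primary outcomes, chiefly GAS. Nothing in the article shows that allocations were in fact anticipated or that scales were adjusted, and the finding does not claim it.

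**What to change.** For any allocations still to be made:

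- The independent schedule holder regenerates the list with randomly varying block sizes, for example 4 and 6, within each ACE-III stratum, and does not disclose the sizes to the interventionist. Certain allocations fall from 25% to about 6%.
- Because best-guess accuracy stays near 68–69%, also finalise and lock the goals and GAS levels before the ACE-III is scored at the same visit. If that order cannot be kept, someone unaware of past allocations could write the GAS levels.

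**Cost:** a regenerated computer list and a fixed order within the baseline visit. The largest possible end-of-trial imbalance is 3 per stratum (half of a block of 6), no larger than under the present scheme.

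The Abstract says registration on 1 November 2021 came three months after the start, so the trial was already under way; whether allocations remain is not stated. If enrolment is complete, report who knew the block size and when, and state the predictability as a limitation of the goal-based outcomes.

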**Figure 1. fig1-00084174231156287:**
[figure not shown]
CONSORT style study flowchart.

This study conforms to the recommendations made by Biundo et al. (2017) for cognitive rehabilitation trials for people with PD where feasible. Recommendations include cognitive profiling, cognitive domains targeted, randomization methods, optimal delivery of neuro-rehabilitation approach, important outcome measure domains, and inclusion/exclusion criteria.

This study involves a person with PD as a consumer from the beginning of the research process to enhance the relevance and usefulness of the research to people with PD (Graham et al., 2018). The involvement of the consumer in this study was from the initial stages and discussions about roles was guided by the involvement matrix tool (Smits et al., 2020) which describes five roles: Listener, Co-thinker, Advisor, Partner, and Decision maker. Collaboratively agreed-upon roles for this project included Advisor and Co-thinker.

The intervention will take place in each participant's home environment in Brisbane, Australia. The first author, an experienced clinician with adult neurological populations trained in CO-OP approach (Polatajko et al., 2001) will collect the data and administer the intervention. The masked assessor is an experienced clinician who did not deliver the intervention and is masked to treatment condition and phase.

